
**Fig. 1 Fig1:**
[figure not shown]
Only patients who achieve a 25% or more reduction in BDI-II or HAM-D scores [36] will be randomly assigned to one of two conditions (CCT or active control)

**Fig. 2 Fig2:**
[figure not shown]
**a.** Study flow before randomized condition assignment. **b**. Study flow after randomized condition assignment

**Table 1 Tab1:** World Health Organization Trial Registration Data Set

Data category	Information
Primary registry and trial identifying number	Clinicaltrials.gov: NCT04383509
Date of registration in primary registry	12 May 2020
Secondary identifying numbers	NA
Source(s) of monetary or material support	King Baudouin Foundation Ghent University University Hospital Ghent
Primary sponsor	Ghent University
Secondary sponsor(s)	University Hospital Ghent
Contact for public queries	[name] [name], [contact]
Contact for scientific queries	[name] [name], [contact]
Public title	RCT for Electroconvulsive Treatment Followed by Cognitive Control Training (ECT-CCT)
Scientific title	Cognitive remediation following electroconvulsive therapy in patients with treatment resistant depression: randomized controlled trail of an intervention for relapse prevention – Study Protocol
Countries of recruitment	Belgium
Health condition(s) or problem(s) studied	Depressive relapse following succesful electroconvulsive treatment (ECT) Cognitive functioning post-ECT
Intervention(s)	Active comparator:cognitive control trainingPlacebo comparator: training without focus on cognitive control
Key inclusion and exclusion criteria	• Ages eligible for study: ≥18 yearsSexes eligible for study: bothAccepts healthy volunteers: no**Inclusion criteria**: age between 18 and 70 years old, current major depressive episode with treatment resistance, eligibility and consent for ECT treatment, ability to provide consent to study **Exclusion criteria**: neurodegenerative disorder or Montreal Cognitive Assessment (MOCA) < 18, catatonia, schizophrenia, alcohol use disorder in previous year, prior ECT treatment, insufficient computer knowledge or analphabetism
Study type	InterventionalAllocation: randomizedIntervention model: parallel assignmentMasking: double blind (Participant, Outcomes Assessor)Primary purpose: treatment
Date of first enrolment	June 2020
Target sample size	88
Recruitment status	Recruiting
Primary outcome(s)	Change in severity of depressive symptoms, clinician-rated (HAM-D) Change in severity of depressive symptoms, self-reported (BDI-II) Change in depressive symptoms and quality of life, self-reported (RDQ) Time Frame:1–7 days before first ECT session, 1–7 days post ECT completion, 1–7 days after intervention/placebo completion, 3 months after ECT completion, and 6 months after ECT completion
Key secondary outcomes	Subjective memory complaints (SSMQ) Time Frame:1–7 days before first ECT session, 1–7 days post ECT completion, 1–7 days after intervention/placebo completion, 3 months after ECT completion, and 6 months after ECT completion Quality of Life in Depression Scale (QLDS) Time Frame:1–7 days before first ECT session, 1–7 days post ECT completion, 1–7 days after intervention/placebo completion, 3 months after ECT completion, and 6 months after ECT completion Rumination (RRS-10) Time Frame:1–7 days before first ECT session, 1–7 days post ECT completion, 1–7 days after intervention/placebo completion, 3 months after ECT completion, and 6 months after ECT completion Cognition (CANTAB) Time Frame:1–7 days before first ECT session, 1–7 days post ECT completion, 1–7 days after intervention/placebo completion, 3 months after ECT completion, and 6 months after ECT completion Cognition (Paced Auditory Serial Addition Task - PASAT) Time Frame:1–7 days before first ECT session, 1–7 days post ECT completion, 1–7 days after intervention/placebo completion, 3 months after ECT completion and 6 months after ECT completion Acceptability and satisfaction: Qualitative interviews Time Frame: 1–30 days after CCT training completion Time to relapse Time Frame:Up to 6 months monitoring Facial features from video footage Time Frame:2 weeks during CCT or placebo intervention

**Table 2 Tab2:** Summary of protocol amendments

Protocol version	
1. December 2017	Original
2. August 2018	Qualitative interviews added
3. December 2019	Overall changes to protocol - Changes in outcome parameters (SSMQ, RDQ) - Changes to aPASAT training - Inclusion of facial videotaping - Extension of study duration

#### Intervention group

Patients in the intervention group will start the CCT training after completion of ECT with a maximum time interval of 7 days. They will perform ten sessions of the adaptive PASAT (aPASAT) on a computer in the clinical center, completing five sessions per week (400 trials per session) for a period of 2 weeks using Inquisit 5 (Millisecond, 2016). During the adaptive PASAT, participants are confronted with a continuous stream of digits (auditory; 1–9), during which they continuously need to respond to the sum of the last two heard digits. The task starts using an inter-trial interval (ITI) of 4000 ms. Every four consecutive correct responses, the ITI decreases with 100 ms, reflecting an increase in task difficulty. Vice versa, following four consecutive incorrect responses, task difficulty decreases as shown by an increase in ITI of 100 ms. Throughout the CCT task, facial video footage will be collected. Patients who complete at least 6 CCT sessions will be regarded as CCT-completers. Patients who fail to complete more than half of the CCT sessions will be excluded. To date there is no data indicating the minimum amount of completed aPASAT training sessions for optimal results.

#### Control group

Patients in the control group will start an active placebo training after completion of ECT with a maximum time interval of 7 days. The active placebo task consists of a speed of response task that shows high similarity to the experimental condition but lacks training of cognitive control. That is, participants are confronted with a continuous stream of digits (auditory; 1–18) and are instructed to immediately respond to the most recently heard digit [37]. Prior research confirmed that this condition controls for non-specific effects of the training and motivational issues [37, 38]. Patients will perform the sessions on a computer, and complete five sessions per week (400 trials per session) for a period of 2 weeks during which facial video footage will be collected.

#### Participant retention and withdrawal

Once a participant is randomized, investigators will make every reasonable effort to follow the patient for the entire 6-month follow-up period. During the cognitive control training patients will be motivated daily by researchers to complete their training. Participants have 14 days to complete 10 training sessions. The rate of loss-to-follow-up is estimated at 5 to 10% after completion of ECT treatment. Systematic methods and reminders for contacting patients, scheduling appointments, and monitoring retention will be developed by the study site.

Participants may withdraw consent for study participation for any reason at any time. For participant safety reasons, investigators may also withdraw participants from the study at any time. In case of non-adherence or non-retention, a final outcome assessment will be planned, if possible, collecting following data; SSMQ, BDI-II, HAMD, RDQ, RRS-10, QLDS and reasons for non-adherence or non-retention.

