### Procedure

Outcome assessors and/or ECT-physicians will provide adequate verbal and written information regarding the study to all eligible patients at the ECT-clinic. Researchers will obtain written informed consent from all patients willing to participate and able to give consent. After consenting to participate and before the start of ECT treatment, all patients will complete baseline cognitive function assessment (CANTAB, PASAT), cognitive complaints (SSMQ), depressive symptomatology (BDI-II, HAM-D), depressive status (RDQ), rumination (RRS-10) and quality of life (QLDS). After ECT completion, cognitive functioning (CANTAB, PASAT), cognitive complaints (SSMQ), depressive symptomatology (BDI-II, HAM-D), depressive status (RDQ), rumination (RRS-10) and quality of life (QLDS) will be assessed. Moreover, all patients will receive standard clinical care. Patients will receive standard pharmacological relapse prevention, under the responsibility of their treating physician, started during (nortriptyline) or after (lithium) ECT by combining nortriptyline (50-150 ng/ml) and lithium (≥0.5 mmol/l) for MDD and lithium (≥ 0.5 mmol/l) alone for BDD. In case of contra-indication for nortriptyline and/or lithium, alternative relapse prevention options will be explored by the treating physician. As is standard clinical care, monthly lithium dosing and testing of renal and thyroid function will be performed by the treating physician. If renal function deteriorates during follow-up this should be reported as an adverse event and may necessitate lithium discontinuation. Before dismissal from the ward participants will receive a two-session CBT-based relapse prevention group therapy and individual counseling by a social worker. Only patients who achieve a 25% or more reduction in BDI-II or HAM-D scores [36] will be randomly assigned to one of two conditions (CCT or active control), see Fig. 1 as cognitive control training has evidence as a relapse prevention strategy and not as a treatment for MDE. Non-responders to ECT will be excluded to allow further clinical treatment for MDE outside of this study protocol. After completion of the CCT, relapse of depression will be monitored for a period of 6 months using mobile assessments of depression (every 2 weeks) and telephone interviews in case of possible relapse. If there is an indication of relapse, patients will be assessed by the semi-structured Mini International Neuropsychiatric Interview (MINI v7.0.0) depressive episode module (A) and referred for psychiatric assessment to their treating psychiatrist for adequate clinical care if necessary. Patients who relapse will be excluded only if they receive a subsequent ECT-course as this might affect cognitive parameters. At three and 6 months, a more extensive evaluation will be performed investigating cognitive parameters (SSMQ), depressive symptomatology (BDI-II, HAM-D), depressive status (RDQ), rumination (RRS10) and quality of life (QLDS). We refer to Fig. 2 for an overview of the study design and Table 1 for the trial registration data set.

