### Data management and analyses

Participant files, including informed consent forms, will be stored in a locked cabinet with restricted access for a period of 20 years after study completion.

We will use a 4 (time: T2, T3, T4, T5) by 2 (condition: active placebo CCT; real CTT) repeated measures design. The significance level will be set at α = .05.

For our main analyses, we will rely on intention-to-treat analysis (ITT) to model effects of CCT on the outcome measures of interest, using the Last-Observation-Carried-Forward (LOCF) method to handle missing data (due to non-response, drop-out or relapse of depression). Where adequate, effects of CCT on our cognitive measures and questionnaire data will be modeled using repeated measures Analysis of Variance (ANOVA) or Covariance (ANCOVA). Significant interaction effects will be further explored using independent and paired samples *t*-tests. Effects of CCT on relapse of depression will be modeled using a Pearson Chi-Square test. In addition, we will conduct survival analyses (Kaplan Meier estimator) to model time to relapse, using the log-rank test to compare the obtained survival curves.

Qualitative data analyses methods will be used to analyze the interviews regarding satisfaction, acceptability, and appropriateness of the design.

Exploratory analyses will be used to investigate the facial video footage data collected during the ten sessions of CCT or active placebo. From the footage, we will deduce facial landmarks and reactions during the performance of the training as an indication of frustration, engagement and general mood, whereas different factors could be of influence on the effectivity of the training. More specifically, we expect to see differences in, e.g., general facial valence, facial muscle tension and frustration.

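### The protocol does not separate stopping training from leaving the study, so 3-month, 6-month and relapse data can end for randomised patients who only stopped training

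*Protocol article*

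**What the plan says.** All references are to the Protocol article.

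- *Participant retention and withdrawal* opens with a commitment that does not depend on adherence: "Once a participant is randomized, investigators will make every reasonable effort to follow the patient for the entire 6-month follow-up period".
- The same section then states: "In case of non-adherence or non-retention, a final outcome assessment will be planned, if possible". The listed content is SSMQ, BDI-II, HAM-D, RDQ, RRS-10 and QLDS. No time point is given, and the MINI depressive episode module, which decides relapse elsewhere in the protocol, is not listed.
- It also provides that "For participant safety reasons, investigators may also withdraw participants from the study at any time". The withdrawal is from the study, not only from training.
- *Intervention group*: "Patients who fail to complete more than half of the CCT sessions will be excluded". The text does not say whether this means exclusion from follow-up, from the analysis or from both. The *Control group* section has no matching sentence.
- *Procedure* starts relapse monitoring after completion of the training. On relapse it says: "Patients who relapse will be excluded only if they receive a subsequent ECT-course as this might affect cognitive parameters".
- Table 1 sets the post-training assessment at "1–7 days after intervention/placebo completion", but dates the 3- and 6-month assessments from completion of ECT.
- *Data management and analyses*: "we will rely on intention-to-treat analysis (ITT) to model effects of CCT on the outcome measures of interest", with last observation carried forward for missing data.

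**The concern.** Not adhering to training and not staying in the study are different events. A patient can stop the computer sessions and still answer a fortnightly text message and attend two visits. The protocol joins the two events and attaches to both an assessment that it calls final. Site staff could reasonably take this as an instruction to close the patient's data collection.

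If they do, follow-up is cut by behaviour that occurs after randomisation and that may differ between arms, since one task adapts its speed to performance and the other asks only for the digit just heard. An intention-to-treat comparison needs outcomes on everyone randomised, whatever they did with the training. Relapse is the outcome most exposed: it is the basis of the sample size and is analysed by chi-square and log-rank tests. Six-month relapse data that were never collected cannot be recovered at the analysis stage.

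**Working it through.** **1. The passages side by side.**

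| Item | Depends on completing training? | Where |
|---|---|---|
| Six-month follow-up commitment | No, runs from randomisation | Participant retention and withdrawal |
| Single final assessment | Triggered by non-adherence | Participant retention and withdrawal |
| Exclusion for few sessions | Yes | Intervention group |
| Start of relapse monitoring | Yes | Procedure |
| Post-training visit (T3) | Yes | Table 1 |
| 3- and 6-month visits (T4, T5) | No, dated from ECT completion | Table 1 |
| Intention-to-treat analysis | No | Data management and analyses |

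A patient who stops after, say, four of the ten sessions is to be followed for six months under the first row. Under the second and third rows the same patient gets one undated assessment and is excluded. Taken literally, the patient also has no defined T3 date and no defined start of relapse monitoring.

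**2. The plan's own figure.** For a Pearson chi-square test with w = 0.3, alpha 0.05 and 1 degree of freedom, the noncentrality is N × w² = 88 × 0.09 = 7.92, giving power 0.804; N = 87 gives 0.799. The stated N = 88 reproduces and is not in question. If the stated 5 to 10% loss to follow-up came out of the 88, 84 to 79 patients would have relapse data (88 × 0.95 = 83.6; 88 × 0.90 = 79.2), with power 0.785 to 0.760.

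**3. Illustration of possible bias in relapse.** No non-adherence rate is given, so the inputs are partly assumed:
- overall relapse risk r = 37.7% in both arms, no true effect (six-month rate under pharmacotherapy, *Background*);
- share stopping s = 15% in one arm and 5% in the other (assumed);
- stoppers' relapse risk k = 37.7% (average) or 60% (assumed);
- all relapses among stoppers go unseen (assumed).

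Stoppers counted as not relapsed: observed rate = r − s × k.
- k = 37.7%: 0.377 − 0.15 × 0.377 = 32.0%, against 0.377 − 0.05 × 0.377 = 35.8%. Difference 3.8 points.
- k = 60%: 0.377 − 0.090 = 28.7%, against 0.377 − 0.030 = 34.7%. Difference 6.0 points.

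Stoppers removed from the denominator: observed rate = (r − s × k)/(1 − s).
- k = 37.7%: 37.7% in both arms. Difference 0.
- k = 60%: 0.287/0.85 = 33.8%, against 0.347/0.95 = 36.5%. Difference 2.8 points before rounding.

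The range is therefore 0 to 6 points for this one stopping pattern. The arm with more stopping looks better. If that is the placebo arm, the error runs against the training.

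**4. Scale against chance error.** With 44 per arm (88/2) and 37.7% relapse, the standard error of the difference is √(2 × 0.377 × 0.623/44) = 0.103, about 10 points. The illustrated bias is smaller than one standard error but, unlike chance error, is systematic.

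**The case against.** The strongest reply is that no sentence says follow-up stops when training stops. The section opens by promising six months of follow-up, and the final assessment can be read as a fallback for patients who cannot be kept. This stands: the text is in conflict with itself, and it is not a flat rule that ends follow-up. The promise does not settle the matter, though, because the later sentence names non-adherence as a trigger in its own right and the Intervention group section adds exclusion.

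A reader might also infer that the patients lost are those most likely to worsen, particularly through safety withdrawals. The documents do not support that. *Procedure* keeps relapsed patients in the study unless they receive another ECT course, and relapse leads to referral to the treating psychiatrist, not to withdrawal. The link is plausible but neither stated nor quantified.

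Third, intention-to-treat with the last value carried forward keeps these patients in the scale analyses. That is so, but the value is imputed, and the method gives no relapse status or relapse time.

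Fourth, the 15% assumed above exceeds the only attrition figure given, 5 to 10%. That figure is for loss to follow-up and may not cover patients excluded for few sessions, so it does not bound the problem. Censoring stoppers in the Kaplan-Meier analysis would likewise remove the bias if their risk is average, but not otherwise.

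Finally, an article may leave discontinuation procedures to the full protocol. Missing detail would be no finding; here the printed rules disagree with one another.

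**Conclusion.** The point holds as a conflict within the protocol. Taken together, the retention section, the Intervention group exclusion and the timing of T3 and relapse monitoring can end 3-month, 6-month and relapse data collection for randomised patients who only stopped training. This contradicts the six-month commitment and the intention-to-treat analysis. Scale scores would be imputed; relapse status and time to relapse would be unobserved.

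Neither the direction nor the size of any bias can be derived from the documents. The 0 to 6 points rest on assumed stopping of 15% against 5%, an assumed stopper risk of 37.7% or 60%, and a choice between counting stoppers as not relapsed and removing them. They do not show a bias in favour of the training. The sample size of 88 is not affected. The change is worth making because it is cheap and the data cannot be collected afterwards.

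**What to change.** In *Participant retention and withdrawal*, define stopping training and withdrawing consent for follow-up as separate events. For every randomised patient in either arm who has not withdrawn consent for data collection, keep the fortnightly relapse screen and the T3, T4 and T5 assessments. Reserve the final assessment for patients who leave the study.

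Date T3 and the start of relapse monitoring from a point that every randomised patient has, such as the end of the 14-day training window. T4 and T5 need no change, because they already run from ECT completion.

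Reconcile *Procedure*, *Intervention group*, *Participant retention and withdrawal* and *Data management and analyses* accordingly. State what exclusion means in each place, and whether patients withdrawn by investigators on safety grounds still contribute outcome data. The clinical decision to withdraw a patient is outside this comment.

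The cost is protocol wording and some extra effort to contact patients who have stopped training. The visits are already scheduled and the screen is a text message with a telephone call where needed.

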In an extensive meta-analysis that included 84 within-subjects designed studies (a total number of almost 3000 subjects and 24 different cognitive variables) using optimal stimulation parameters, Semkovska & McLoughlin found a short-term decrease in a broad range of cognitive control processes [13]. Cognitive control refers to processes that allow information processing and behavior to vary adaptively and flexibly depending on current goals [14], and includes a broad class of mental operations such as (working) memory, attention, and concentration. These cognitive deficits remain within 3 days following ECT treatment, followed by recovery in the two subsequent weeks except from deficits in episodic retrograde (i.e., autobiographical) memory. Most importantly, these cognitive side effects of ECT, even though transient, might trigger mechanisms that increase relapse in depressed patients. Indeed, based on the available cross-sectional, prospective and longitudinal research, reduced cognitive control is an important neurobiologically driven vulnerability factor for depression (for a review, see De Raedt & Koster, 2010) [15]. Intensive research has shown that deficient cognitive control is a crucial vulnerability factor for recurrent depressive episodes. Moreover, repetitive negative thinking (RNT) is a key vulnerability mechanism in depression and research suggests that the inability to interrupt RNT is linked to inadequate cognitive control [16–19].

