### Hypotheses

On our primary outcome measure, depressive symptomatology as measured by HAM-D, BDI-II and RDQ, we expect a reduction in patients that received 2 weeks of CCT as compared to the active placebo condition following ECT. On our secondary outcome measures we expect [1] reduced cognitive complaints (SSMQ), [2] improved cognitive functioning (CANTAB, PASAT), [3] reduced rumination (RRS-10, 4) enhanced quality of life (QLDS) in patients that received the cognitive control training compared to active placebo. These effects are expected immediately after the CCT as well as within the 6 months follow up period. Beneficial effects will also be reflected in reduced risk for relapse of depression during the period of 6 months follow-up. Moreover, we expect more positive treatment evaluations by both patients and their peers, increased patient satisfaction and acceptability of ECT in patients that received CCT as compared to an active placebo condition following clinical response ECT.

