#### Cognitive functioning

##### CANTAB

In order to assess the patients’ cognitive functioning, three tests of the Cambridge Neuropsychological Test Automated Battery (CANTAB®) were selected to cover (working) memory and executive functioning: Pattern Recognition Memory (measuring visual pattern recognition memory) and One Touch Stockings of Cambridge (measuring spatial spanning and working memory). A third test, Motor Screening was included to measure general sensorimotor skills. CANTAB® tests will be measured before ECT, after ECT, and after CCT completion (Fig.1).

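### The exit assessment omits CANTAB and PASAT, so LOCF records patients who leave before the post-training test as having no cognitive recovery

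*Protocol article*

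**What the plan says.** Under Participant retention and withdrawal, the article plans an exit visit for non-adherence or non-retention at which "a final outcome assessment will be planned, if possible, collecting following data; SSMQ, BDI-II, HAMD, RDQ, RRS-10, QLDS and reasons for non-adherence". Compared with the post-ECT battery in the Procedure section, only CANTAB and PASAT are missing. The Hypotheses section names these two as a secondary outcome with an expected difference between arms: "improved cognitive functioning (CANTAB, PASAT".

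Data management and analyses makes the main analysis intention-to-treat, "using the Last-Observation-Carried-Forward (LOCF) method to handle missing data (due to non-response, drop-out or relapse of depression". It puts the cognitive outcomes in the same framework: "effects of CCT on our cognitive measures and questionnaire data will be modeled using repeated measures Analysis of Variance (ANOVA) or Covariance (ANCOVA".

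On timing, the CANTAB section states that "CANTAB® tests will be measured before ECT, after ECT, and after CCT completion", and Table 1 sets the two visits that matter here at "1–7 days post ECT completion, 1–7 days after intervention/placebo completion". On the natural course, the Background reports: "These cognitive deficits remain within 3 days following ECT treatment, followed by recovery in the two subsequent weeks", with autobiographical memory as the exception. On attrition, the retention section states: "The rate of loss-to-follow-up is estimated at 5 to 10% after completion of ECT treatment".

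**The concern.** LOCF assumes that an outcome stays where it was last seen. For CANTAB and PASAT the protocol's own Background says otherwise: the period between the post-ECT test and the post-training test is when cognition is expected to recover, whichever arm the patient is in. A patient who leaves in that period has no later cognition value, because the exit visit does not ask for one, and is analysed as if no recovery took place.

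What is at stake is the secondary hypothesis on objective cognition. Recovery is understated within each arm. A real benefit of CCT is diluted. If one arm loses more patients during training than the other, natural recovery that went unrecorded appears as a treatment difference. A test that was never taken cannot be restored at analysis, so this has to be settled in the visit schedule.

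**Working it through.** **The plan's own figure.** The Sample size calculation reproduces: (1.960 + 0.842)² / 0.3² = 87.2, rounded up to 88, with power 0.804 at 88. This point does not dispute it. The 88 serves only as a base for counting patients.

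**Timeline in days after ECT.**
- Post-ECT test: days 1 to 7 (Table 1).
- Recovery according to the Background: from about day 3 to about day 3 + 14 = 17.
- Training starts within 7 days of ECT (Intervention group, Control group), and patients have 14 days to finish (Participant retention and withdrawal). For a patient who uses the whole window, training ends on about days 14 to 21.
- Post-training test: 1 to 7 days later, so about days 15 to 28.

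The carried-forward value thus comes from the deficit or the early part of recovery. The value it replaces would come from the end of recovery or later.

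**Number of patients.** 0.05 × 88 = 4.4 and 0.10 × 88 = 8.8, so about 4 to 9. This is an upper bound on those lost to follow-up, because it puts all loss after ECT before the post-training test.

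**Size of the distortion.** Neither of the following is in the documents; both are assumptions:
- R, natural recovery between the two tests: 0.3 to 1.0 SD.
- D, true CCT effect on cognition: 0, 0.3 or 0.5 SD.

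Let d_CCT and d_pl be the shares lost before the post-training test. Suppose that leavers would have recovered and responded like those who stay. LOCF gives each leaver a change of zero, so the estimated difference in change is

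(1 − d_CCT)(R + D) − (1 − d_pl)R = (1 − d_CCT)D − (d_CCT − d_pl)R.

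- Equal 10% loss, D = 0: the estimate is 0, so there is no bias.
- Equal 10% loss, D = 0.3: 0.9 × 0.3 = 0.27. With D = 0.5: 0.9 × 0.5 = 0.45.
- 10% CCT against 5% placebo, D = 0: −0.05 × 0.3 = −0.015 to −0.05 × 1.0 = −0.05 SD.
- 10% CCT against 0% placebo, D = 0: −0.10 × 0.3 = −0.03 to −0.10 × 1.0 = −0.10 SD.
- 5% CCT against 10% placebo, D = 0: +0.015 to +0.05 SD.
- 10% CCT against 5% placebo, D = 0.3: 0.27 − 0.015 = 0.255 to 0.27 − 0.05 = 0.22 SD.

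Within an arm, mean recovery is understated by d_CCT × (R + D) on CCT and by d_pl × R on placebo. At 10% loss on placebo that is 0.03 to 0.10 SD.

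**The case against.** The case on the other side has several parts, and much of it stands.

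- **The loss rate is not a rate of leaving during training.** The 5 to 10% covers the whole period after ECT, including six months of follow-up. Anyone lost after the post-training visit already has the cognition values. This stands, and is why 4 to 9 is an upper bound. The exit visit is also triggered by non-adherence, which that rate does not count.
- **The 88 are completers.** The Sample size calculation recruits until 88 patients have completed the training, so early leavers come on top of the 88. This stands for the count. The distortion depends on shares of those randomised, so the SD figures do not change.
- **Some early stoppers may be excluded.** The Intervention group section excludes patients who miss more than half of the sessions, whereas the analysis section promises intention-to-treat. If the exclusion is applied to the analysis, those patients are dropped and not carried forward. This stands. The two passages must be reconciled before the number carried forward is known.
- **The exit visit may not replace the scheduled one.** A reader might infer that everyone who stops training gets only the exit list. The article does not say so, and it promises reasonable effort to follow every randomised patient for six months. Against that, the post-training visit is timed from completion, which an early stopper does not reach, and no other date is given. The gap is certain only for patients who leave the study.
- **The post-ECT value is not always the lowest point.** By the Background's account, a patient tested on days 4 to 7 is already recovering. This stands; the smaller values of R allow for it.
- **A short exit battery spares patients who are leaving.** That is a fair trade-off, but it leaves one hypothesis without data from them.

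Table 1 also lists CANTAB and PASAT at 3 and 6 months, whereas the Procedure and CANTAB sections do not. If those visits take place, an early stopper who stays in follow-up would be tested later, but for one who has left the study the post-ECT value would be carried further still.

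**Conclusion.** The point holds as a small, avoidable weakness in the secondary cognition outcomes. The omission is explicit in the exit list, LOCF for drop-out covers the cognitive measures, and the Background expects change over the interval that LOCF treats as flat.

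The number affected is at most about 4 to 9 of 88 if all of the expected loss falls before the post-training visit. With no true effect, loss differences of 5 to 10 percentage points give a false difference of about 0.015 to 0.10 SD. A true effect is shrunk in addition by the share lost on CCT, for example from 0.3 to 0.27 SD at 10%. These sizes rest on an assumed recovery of 0.3 to 1.0 SD and on leavers behaving like stayers. If leavers would have gained less from CCT, the shrinkage is smaller.

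A reader might go further and infer a bias against CCT because its task is harder. The documents give no loss rates by arm, and the sign reverses if placebo loses more. Nor do they support placing all 9 losses in one arm of 44. The primary outcome measures HAM-D, BDI-II and RDQ are on the exit list, so this omission does not touch them, and the sample size is unaffected.

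**What to change.** Make two changes to Participant retention and withdrawal:

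1. Add CANTAB and PASAT to the exit list, to be given after the depression measures so that a patient who tires has already supplied those.
2. State that patients who stop training early are still invited to the post-training assessment when it would have taken place: the end of the 14-day training window plus 1 to 7 days, that is, days 15 to 21 counted from the start of that window. Use the exit visit only for those who will not return.

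The second change matters as much as the first, because a test given shortly after stopping would still catch incomplete recovery. The passage that excludes patients with few sessions should also be reconciled with the intention-to-treat statement, so that it is clear whose values are carried forward.

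The cost is two assessments already used in the trial, for a handful of patients, and a sentence or two of text. The downside is a longer final visit, which some leavers will decline. LOCF would still apply to them.
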